### The intervention

Participants in all intervention groups will receive a 200-ml bottle of Genestra brand Super EFA Forte Liquid Omega-3 Fatty Acid. Participants will be instructed to take 1 teaspoon a day with a meal.

Participants in the Gutopia and Gutboost intervention groups will receive HMF Maternity Probiotic Formula, a Genestra brand. Participants will be asked to take one tablet daily with food.

Details of both supplements are provided under Investigational products in the following section.

Only participants in Gutopia will receive a dietary intervention. Intervention is geared toward increasing gut-friendly foods via a flexible dietary plan aimed at increasing daily uptake of prebiotic and probiotic foods. A registered dietitian will use baseline food questionnaire data provided by each subject at enrollment to devise strategies and recommendations for increasing intake of pre/probiotic foods. The target goal is to include at least 35 g/day of fiber and at least one to two servings of fermented foods daily. The dietary intervention will also include recommendations minimizing highly processed foods high in sugar and fat. To improve adherence and accountability, weekly follow-ups by phone, virtual meeting, or email will be conducted by a trained study team member until patients have reached a level of confidence in attaining goals. During each follow-up, the study team will monitor the level of adherence to the study RD’s recommendations. These follow-ups will be designed to provide encouragement while helping patients address and prevent triggers that jeopardize their fiber intake.

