### Objectives

The main objective of this study is to assess the feasibility and acceptability of a combination of nonpharmacological interventions—a high-fiber diet, probiotics, and fish oil supplementation—in currently stable pregnant women with a history of depression and or anxiety. This population has specifically been chosen because a history of mood or anxiety disorders is the strongest predictor of PDA (4).

This study will also aim to understand the ease of recruitment, protocol adherence, and treatment compliance in this cohort. The findings of these objectives will inform on strategies needed to build a larger trial aimed at comparing the efficacy of these interventions and the magnitude of change and impact of the microbiome and PDA.

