## Methods

### Trial design and setting

This is a single-centered, partially randomized placebo-controlled double-blind feasibility trial with three intervention arms (Gutopia, Gutboost, and Gutless) and one active control. In total, 100 pregnant women with a history of depression and/or anxiety/PDA attending Sunnybrook Hospital Clinics in the Greater Toronto Area will be recruited.

Participants in Gutopia will receive a daily dose of both investigational products and dietary counseling on increasing dietary fiber. Participants in Gutboost will receive a daily dose of both investigational supplements, while participants in the Gutless arm will receive fish oil and a placebo. Participants in Gutless and Gutboost will be blinded to the status of the placebo/probiotic they will be receiving. The study member interacting with the patients will also be blinded to the treatment group the participant is assigned to. Participants who fully consent to receiving both investigational products, including placebo, will be fully randomized to one of the intervention arms. Participants not willing or able to take a placebo or probiotics will be assigned (not randomized) to the appropriate group that accommodates their preferences/needs. Participants unable or unwilling to take any of our investigational products will be assigned to the active control arm. Women in the control arm will receive standard care offered to all obstetric patients seen at the hospital.

The study involves six study visits, all of which can be conducted virtually every 3 months from the time of enrollment (**Figure 1**). The last study visit will happen between 9 and 12 months postpartum. Two of the study visits will occur during pregnancy [enrollment (visit 1) and third trimester (visit 2)], with the remaining occurring at 1, 3, 6, and 9 months postpartum. At all study visits, information on diet, mental health, physical activity, and sleep quality will be collected. Additionally, all participants will provide a stool sample at each visit, using our stool collection kits, which will be shipped to or dropped off at our center.

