#### Use of theory

Given the nature of this feasibility study, we aim to promote increased accountability with regular follow-ups to drive change. To achieve this, theoretical proponents of motivational interviewing will be incorporated into study visits. For instance, behavior change will be enabled by causing participants to verbalize arguments for changes and decrease language that favors the status quo. Furthermore, relational factors, such as expressions of empathy, will be used to promote positive change (25).

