#### Outcomes measured

As a feasibility study, process evaluation will be our primary outcome. In the first 6 months of the trial, we will monitor the number of patients screened, randomized, and enrolled per month; the average time lapse between screening and enrollment; and the time taken to enroll 15% of our target (i.e., *n* = 15). We will also assess baseline rates of O3FA and probiotics supplementation in this specific cohort prior to randomization. We will identify and document all barriers to meeting the target numbers needed for each study arm and address them appropriately. In patients successfully enrolled, we will also monitor compliance, side effects, and challenges in taking supplements in the intervention groups. We will closely document all issues in adhering to intake instructions and attempt to resolve them on a case-by-case basis (i.e., if forgetfulness is a cause, daily automatic email reminders will be sent to that individual). In Gutopia, attaining a daily fiber target of 35 g/day will be monitored frequently via phone call in the first 6 months or until the patient no longer needs the support. Finally, we will assess retention rates, the proportion of study visits completed, and challenges related to the collection and shipment of stool samples, as well as the completion of questionnaires and dietary recall. All barriers to the timely completion of these tasks will be documented and managed on a case-by-case basis. Strategies to overcome each of these barriers will be proposed in the final write-up of this study.

As part of our secondary aims, we will seek the opportunity to produce preliminary data on the association between maternal microbial response to each intervention and self-reported scores on questionnaires of mental health challenges. This will be for exploratory purposes to identify any signals that will further support the conduct of a larger trial.

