## Discussion

Given the prevalence of PDA and its resulting impact on quality of life and infant well-being, the importance of investigating underutilized and overlooked nonpharmacological options is paramount. Specifically, the need to investigate alternative approaches in comparison to prescription medication and psychotherapy has been identified as an important need by expecting and new mothers. It is anticipated that pregnant women with a history of depression and anxiety will be particularly interested in partaking in this trial, resulting in favorable recruitment rates. Given the positive findings of O3FA and probiotic supplements on mental health symptoms in nonpregnant adults, we expect a similar trend in PDA symptoms, with a low likelihood of adverse events.

While not our main objective, we anticipate a correlation between the microbial composition and probiotics and O3FA supplementation. As several recent studies have demonstrated a positive impact of probiotics (19–21) or O3FAs (22, 23) on mental health outcomes via changes in the gut microbiome, this has yet to be demonstrated in individuals at risk of PDA. Having intervention groups that provide both supplements (Gutboost) versus O3FA alone (Gutless) will allow us to determine potential interaction between these supplements. We anticipate a difference in mental health scores between the Gutboost and Gutless intervention groups. Incorporating a third intervention arm where dietary counseling is provided in addition to supplementation (Gutopia) further allows us to understand the interaction between diet and supplementation. We anticipate differences in mental health scores between Gutopia compared to the other intervention arms. Additionally, having an active control arm can potentially inform the magnitude and directionality of these changes by comparing outcomes in the intervention arms (*N* = 75) to the active control arm (*N* = 25).

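### Gutopia versus Gutboost estimates the effect of a whole dietary-counselling package, including weekly supportive contact, and cannot be read as the effect of fibre, of diet alone, or of a diet-by-supplement interaction

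*Protocol article*

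**What the plan says.** All places are in the protocol article.

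- **Arm content** (Trial design and setting): "Participants in Gutopia will receive a daily dose of both investigational products and dietary counseling on increasing dietary fiber". For the comparator: "Participants in Gutboost will receive a daily dose of both investigational supplements".
- **Diet component** (The intervention): given to Gutopia only. The targets are 35 g or more of fibre a day and "at least one to two servings of fermented foods daily", with advice to limit highly processed foods. A dietitian devises the recommendations. In addition, "weekly follow-ups by phone, virtual meeting, or email will be conducted by a trained study team member", continuing until the woman is confident of reaching her goals. These contacts are meant to encourage her and to help with obstacles to fibre intake.
- **Monitoring** (Outcomes measured): phone monitoring of Gutopia's fibre target is repeated here.
- **Behavioural technique** (Use of theory): "theoretical proponents of motivational interviewing will be incorporated into study visits". No arm is named.
- **How the addition is described** (Objectives): the combination under test is "a high-fiber diet, probiotics, and fish oil supplementation".
- **What is to be inferred** (Discussion): the Gutopia arm "further allows us to understand the interaction between diet and supplementation". The section Microbiome and mental health likewise sets out to measure that interaction.

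**The concern.** The label and the intended inference are narrower than the intervention. If Gutopia women report better mood, take their supplements more regularly or stay in the study longer, regular encouraging contact could explain some or all of it, since each of these outcomes can respond to supportive attention. Within the diet itself, fermented foods and reduced processed food change alongside fibre, and fermented foods overlap in kind with the probiotic capsule.

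The process measures are exposed as well as the exploratory mood scores. Compliance, retention and visit completion are among the primary process measures, and the Objectives say the findings will shape a larger trial. Microbiome profiling adds that enrolment will continue into that trial if this stage succeeds. A misnamed contrast would carry forward.

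The motivational-interviewing sentence raises a separate question. If it means the six assessment visits, then Gutboost, Gutless and control also receive a behaviour-change technique, although control is described as receiving standard care.

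**Working it through.** The protocol gives no figure for this point, so there is nothing to reproduce. The check is which effects the four arms can separate.

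**Step 1: code the arms by component.** The inputs come from Trial design and setting, Randomization and baseline evaluation, The intervention, and Use of theory (read literally).

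| Arm | Intercept | Fish oil | Probiotic capsule | Fibre | Fermented food | Less processed food | Weekly contact | Open allocation | Motivational interviewing |
|---|---|---|---|---|---|---|---|---|---|
| Gutopia | 1 | 1 | 1 | 1 | 1 | 1 | 1 | 1 | 1 |
| Gutboost | 1 | 1 | 1 | 0 | 0 | 0 | 0 | 0 | 1 |
| Gutless | 1 | 1 | 0 | 0 | 0 | 0 | 0 | 0 | 1 |
| Control | 1 | 0 | 0 | 0 | 0 | 0 | 0 | 1 | 1 |

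Open allocation is coded 1 for Gutopia because the coordinator is told of assignment to that arm but not which of the other two product arms a woman is in. It is coded 1 for control because control women take no product. Dietitian input is not a separate column; it would be identical to the fibre column.

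**Step 2: take the contrast.** Gutopia minus Gutboost = (0, 0, 0, 1, 1, 1, 1, 1, 0). Five coded elements change at once: fibre, fermented food, less processed food, weekly contact and open allocation.

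**Step 3: ask whether fibre, or diet, can be isolated.** The matrix has 4 rows, 9 columns and rank 4. Adding a row that picks out fibre alone raises the rank to 5, so that effect is not estimable. The columns for the three food elements and for weekly contact are identical, so diet cannot be separated from contact either.

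**Step 4: ask whether the diet-by-supplement interaction can be estimated.** Use columns intercept, fish oil, probiotic, diet, diet × supplement:

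- Gutopia (1, 1, 1, 1, 1)
- Gutboost (1, 1, 1, 0, 0)
- Gutless (1, 1, 0, 0, 0)
- Control (1, 0, 0, 0, 0)

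The rank is 4 with 5 columns. The last two columns are identical because no arm receives the diet without the supplements. Even if contact were matched, the interaction could not be estimated.

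**Step 5: motivational interviewing.** Write D for the diet elements together, C for contact (with open allocation), and M for motivational interviewing.

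- Given equally in all arms: (D + C + M) − M = D + C. It cancels. If it also leads Gutboost women to change their behaviour, the contrast shrinks.
- Given in Gutopia only: D + C + M. It becomes one more element of the package.

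On neither reading is D isolated. On the first reading the effect is dilution, not confounding.

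**The case against.** The strongest reply is that the protocol already names a package. The intervention section openly defines the diet as prebiotic and probiotic foods with both targets stated, and the Discussion speaks of dietary counselling added to supplementation. Counselling implies contact. On this view fermented and less processed foods are the declared diet, not hidden confounders. That stands: they rule out a fibre-only reading, not a diet reading. It does not rescue the attribution to diet apart from contact, or the interaction claim.

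It is also fair that efficacy is not the purpose here. Process evaluation is primary, the mental-health signals are exploratory, and the formal comparison belongs to a later trial. The Outcomes measured section states no between-arm test of compliance or retention. This limits the severity.

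Several stronger readings are tempting but unsupported:

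- **That shared motivational interviewing biases the contrast.** It cancels or dilutes, as shown. The placing of the section, between Gutopia's follow-ups and Gutopia's food tables, suggests it may have been meant for Gutopia only; the sentence itself does not say so.
- **That a contact ratio can be calculated.** A reader might multiply the weekly schedule by the six months named under Outcomes measured. Neither section states such a count, follow-up ends once the woman no longer needs it, and an email is not equivalent to a 45–60 minute visit. The result would be a ceiling, not an estimate.
- **That weekly calls uncover more supplement problems in Gutopia.** The calls are described as checking dietary adherence. Supplement intake is not mentioned there.
- **That the other arms get no support beyond visits.** Adherence problems are handled individually in all intervention groups; for forgetfulness, "daily automatic email reminders will be sent to that individual". What is missing is a scheduled equivalent of the weekly follow-up.
- **That reminders should be made uniform.** This would alter the adherence barriers and solutions that the study sets out to observe.

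**Conclusion.** The point holds as one of attribution. Gutopia versus Gutboost can be read as the effect of a dietary-counselling package that includes contact. It cannot be read as the effect of fibre, as the effect of diet apart from contact, or as evidence on a diet-by-supplement interaction. The last of these fails even without the contact problem, because no arm has diet alone.

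No numerical size can be given, because the protocol fixes neither the number of follow-up contacts nor an expected effect of contact. What can be said is structural: five coded elements change together and one contrast is available, so only their sum is identified.

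The conclusion assumes that arm content is as the article describes, with no matched contact set out elsewhere, and that self-rated mood, compliance and retention can respond to supportive contact. The consequence is modest at this stage. The changes are still worth making now, because the results are meant to inform the larger trial and enrolment may continue into it.

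**What to change.** 1. In Objectives, Microbiome and mental health, and Discussion, state that Gutopia versus Gutboost estimates the effect of the dietary-counselling package: fibre, fermented foods, less processed food, dietitian input and supportive follow-up.
2. In Microbiome and mental health and in Discussion, remove the statements that the design measures or shows the interaction of diet and supplementation.
3. In Use of theory, say that motivational interviewing is delivered only in Gutopia's dietary follow-ups and not in the assessment visits shared by all arms, where EPDS and GAD-7 are collected.
4. Log the contacts made with each woman and report them by arm beside compliance and retention.

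The cost is protocol wording and a small logging burden, with a narrower claim for Gutopia. Arms, sample size and products are unchanged. These changes do not remove the contact imbalance; they name it correctly and make it visible to readers of the results.

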#### Use of theory

Given the nature of this feasibility study, we aim to promote increased accountability with regular follow-ups to drive change. To achieve this, theoretical proponents of motivational interviewing will be incorporated into study visits. For instance, behavior change will be enabled by causing participants to verbalize arguments for changes and decrease language that favors the status quo. Furthermore, relational factors, such as expressions of empathy, will be used to promote positive change (25).

#### Educational material and resources

Participants in the Gutopia arm will be presented with food tables listing common foods, and snacks from different food groups, containing the highest amount of fiber per serving. This is to help enable participants to reach their target daily fiber with the fewest servings possible. These tables are categorized by food group and provide the food names, brands, and recommended serving sizes. These have been provided in the supplemental information section.

#### Investigational products

All participants in treatment groups will receive a 200-ml bottle of Genestra brand Super EFA Forte Liquid Omega-3 Fatty Acid. This product contains a total of 2,600 mg of O3FA (1,500 mg of EPA + 1,000 mg of DHA) per 5-ml serving. The participant will be instructed to take 1 teaspoon a day with a meal. Each bottle contains about 40 servings, and a daily consumption of 1 teaspoon a day is expected to last 6 weeks. Each patient will receive supplies for the duration of the study period. While no clear upper tolerable dose in pregnancy has been identified, no increase in the risk of bleeding or complications at delivery has been observed in pregnant women (*n* = 533) receiving 2.7 g/day during the last trimester compared to women receiving olive oil or no supplements (26, 27). An updated review including 70 RCTs (19,927 participants) indicated a reduced risk of preterm birth for those tasking O3FAs compared to placebo or no intervention (28). The dose used in our trial is consistent with a dose that is likely effective and is below the safe maximum dose suggested in these trials.

We will use HMF Maternity Probiotic Formula, a Genestra brand. Each capsule contains 10 billion of four strains of bacteria: *Lactobacillus salivarius* (6.25 billion CFU), *Bifidobacterium animalis* subsp. *lactis* and *Bifidobacterium bifidum* (2.5 billion CFU), and *Lactobacillus paracasei* (1.25 billion CFU). While an updated review of evidence including seven trials (1,647 participants) indicates a possible increased risk of preeclampsia (29), a meta-analysis of several RCTs of probiotic use in pregnancy reported no increased risk to the fetus (30). Furthermore, the probiotic supplement in our trial was specifically labeled for pregnant women, following its use in a double-blind, placebo-controlled clinical trial of 454 pregnant women—no increase in adverse events in comparison to placebo was noted (31).

The placebo capsules will contain 48% maltodextrin, 48% microcrystalline cellulose, 2% magnesium stearate, and 2% silicon dioxide. The capsule shell will be composed of hydroxypropyl ethylcellulose and will be identical in capsule shape and packaging to the probiotics. Participants will be instructed to take one capsule a day with food, 2–3 hours before or after taking an antibiotic in the event that one is prescribed through ancillary usual care received separate from study procedures. Each box of probiotics/placebo is expected to last 30 days. Participants will be provided with enough supplies for the duration of the study period.

#### Concomitant therapies

All concomitant medication, psychotherapy, or natural health products will be allowed during this trial. Participants will be encouraged to continue all other previous treatments at the same dose for the duration of the trial, if possible, but allowed to make changes if recommended by their mental healthcare provider. Participants will be queried at baseline and at each follow-up visit about their use of medication, psychotherapy, or natural health products, and any changes will be recorded, analyzed, and reported.

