### Rationale for study

Evidence for the positive role of fiber, probiotics, and O3FAs in depression and anxiety is accumulating. Studies on the combination of these supplements and their mitigating effects on the microbiome remain elusive. A significant knowledge gap remains on the usability and efficacy of fiber, probiotics, and O3FAs in the pregnant population, particularly in relation to mental health disorders. Moreover, challenges exist in the design and conduct of randomized controlled trials in pregnancy or the use of complex, combination interventions, making drawing inferences challenging. Given the nonpharmacological nature of the supplements and their wide availability, safety, and cost-effectiveness, they have a high potential to serve as a preferred management option for the prevention or treatment of mental health disease in pregnant and lactating mothers. Demonstrating the relationship in this population is the first step in using an appropriate research design.

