### Participant eligibility

#### Inclusion criteria

A person aged 18–43 years old.At 12–35 weeks of gestation at the time of enrolment.Uniparous pregnancy.A nonsmoker, alcohol, or recreational drug user.Financially stable.In a married or common-law relationship.Clinical diagnosis of lifetime depression/anxiety or PDA (stable since the conception of the current pregnancy).No other significant comorbidities.Ability to read in English and provide informed consent.

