#### Exclusion criteria

Prepregnancy BMI > 30.Low income (unable to afford basic daily needs).Single parents without any kind of family support.Having a child with significant mental/physical disability.Previously diagnosed with other major mental health disorders.Taking prescription medications (other than SSRIs/SNRIs/TCA).Smoking and recreational drug use.Dietary restrictions or allergies to fish oils.Repeated antibiotic use.Women are unable to switch to study brand supplements.Multiparous women with young children (i.e., one or more children less than 4 years of age at the time of delivery).No/low English reading comprehension.

Our inclusion criteria allow for antidepressant/anxiety use. Medication use is an important prognostic factor that can significantly alter mental health outcomes. Hence, the number of patients treated with an antidepressant/anxiolytic needs to be equally distributed among all arms. To achieve this, we will use stratified randomization using two strata (treated vs. untreated) through a computer-generated process using permuted blocks of three and six. The process will be repeated separately for untreated participants.

Preexisting and diagnosed major mental health disorders will be determined at the time of screening using a modified version of the Mini International Neuropsychiatric Interview (MINI). The MINI, conducted by a trained research team member, will allow for confirmation of a history of anxiety/depression and an absence of current anxiety/depression and other major mental health disorders (bipolar, schizophrenia, psychosis, etc.).

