### Sample size, recruitment plan, and prestudy screening

While a consensus on an ‘ideal’ sample size for pilot/feasibility studies has not been reached, our proposed number (*N* = 100) meets the recommendation for best practice for the conduct of pilot trials.

This is a single-center study conducted at Sunnybrook Hospital, in Toronto, Canada. Pregnant patients attending obstetrics clinics or The Women’s Mood and Anxiety Clinic at Sunnybrook Hospital will be informed by their attending healthcare provider about the study, and permission to share their contact number with the research team will be requested. Interested patients will be called by a member of the research team and screened for inclusion/exclusion criteria and their ability/status on O3FA and probiotic intake. Patients not willing or unable to take either supplement will receive information about the control arm of the study. Patients willing to take the study supplements will receive information about the interventional arms of the study and the process of randomization. Participants will also be informed that they may receive a placebo instead of probiotics. This design accommodates patient preferences and expectations and emphasizes the goal of an inclusive, pragmatic study design to generate real-world data.

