##### O3FA and probiotic interaction

The synergism between O3FAs and probiotics has not been defined. We expect that comparing the microbiome between Gutboost and Gutless will yield differences between O3FA alone and O3FA + probiotics on mental health scores.

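### The concomitant-product rule makes no exception for non-study probiotics, so a woman in Gutless may start her own after allocation

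*Protocol article*

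**What the plan says.** The Concomitant therapies section gives a general rule: "All concomitant medication, psychotherapy, or natural health products will be allowed during this trial". It then encourages women to keep their *other* existing treatments stable, lets them change these on their mental healthcare provider's advice, and has use queried at baseline and every follow-up visit, with changes recorded and reported.

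Two further places bear on own-brand products. The Exclusion criteria list "Women are unable to switch to study brand supplements", and the recruitment section has women asked at screening about their omega-3 and probiotic intake. Under Outcomes measured the article adds: "We will also assess baseline rates of O3FA and probiotics supplementation in this specific cohort prior to randomization".

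The comparison at issue is Gutboost (fish oil plus probiotic) against Gutless (fish oil plus placebo), in which participants are blinded to probiotic or placebo. The section O3FA and probiotic interaction expects that this comparison "will yield differences between O3FA alone and O3FA + probiotics on mental health scores". The Discussion says: "Having intervention groups that provide both supplements (Gutboost) versus O3FA alone (Gutless) will allow us to determine potential interaction between these supplements".

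**The concern.** Probiotics are natural health products and also one of the things being tested. A rule that admits every such product therefore admits the test product into the placebo arm. The article's interpretation of Gutboost versus Gutless depends on Gutless being free of probiotic.

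The article itself gives reasons to think new use is possible. The Rationale speaks of the supplements in these terms: "Given the nonpharmacological nature of the supplements and their wide availability, safety, and cost-effectiveness". At recruitment, "Participants will also be informed that they may receive a placebo instead of probiotics". The follow-up is also long.

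At stake is the one contrast with a placebo for the probiotic, on mental health scores and on the microbiome. The microbiome profile is compared between arms at each follow-up, and an outside probiotic acts on it directly. The feasibility outcomes (recruitment, adherence, retention, sample collection) do not depend on this contrast. The Microbiome profiling section, however, plans to continue enrolment into an efficacy stage if the feasibility trial succeeds, so women enrolled under the loose rule could enter that analysis.

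**Working it through.** **Reading the rules together**

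1. *Women already using a probiotic.* Eligibility requires that a woman can switch to the study brand, and the concomitant rule speaks of continuing *other* treatments. Together these imply that her own product is replaced.
2. *Women who start one after allocation.* The eligibility criterion tests ability to switch at entry, and the stability wording concerns treatments already in place. Neither reaches a new product. The general permission does, and no other section withdraws it.
3. *What recording does.* The visit-by-visit query will show how often this happens but does not prevent it. Under the intention-to-treat approach in Statistical analysis, such women stay in Gutless. Adjusting for use that began after allocation would not restore the randomised contrast.

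**Time available for a new start**

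Inputs: the Inclusion criteria allow entry at 12–35 "weeks of gestation at the time of enrolment"; Trial design and setting puts the last visit at 9–12 months postpartum. Delivery at 40 weeks is assumed.

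- Shortest: (40 − 35) + 9 months (39.1 weeks) = 44.1 weeks
- Longest: (40 − 12) + 12 months (52.2 weeks) = 80.2 weeks

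This describes opportunity. It gives no rate of use.

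**Possible size (illustration only)**

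The article gives no usage rate, effect size or power calculation, so there is no figure of the plan's to reproduce. Let the true effect of the study probiotic be 1, and define:

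- q₀, q₁: shares taking an own probiotic in Gutless and Gutboost
- r: effect of the own probiotic in a woman on placebo, relative to the study product
- s: its added effect in a woman already on the study probiotic

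The observed contrast is (1 + q₁s) − q₀r.

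If the own product adds nothing on top of the study product (s = 0), or is not used in Gutboost (q₁ = 0), the contrast is 1 − q₀r, and the sample size needed for the same power is multiplied by 1/(1 − q₀r)²:

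| q₀ | r | Contrast kept | Sample-size factor |
|---|---|---|---|
| 10% | 0.5 | 0.95 | 1.11 |
| 20% | 0.5 | 0.90 | 1.23 |
| 10% | 1 | 0.90 | 1/0.81 = 1.23 |
| 20% | 1 | 0.80 | 1/0.64 = 1.56 |

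If effects add fully (s = r) and use is equal in the two arms (q₁ = q₀), the contrast is 1.00 and nothing is lost. If s = r and use is higher in Gutboost, it exceeds 1. Dilution is the expected direction but is not guaranteed.

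**The case against.** The strongest reply has four parts.

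- **Existing users are covered.** This stands. A reader might infer from the blanket rule that a woman in Gutless may simply carry on with her own probiotic. The switching criterion and the word *other* point the other way, so the point is confined to new use.
- **The article condenses a fuller protocol.** Participant instructions are often left to that document. Here, though, the article does not stay silent: it states a rule covering all such products, and an unshown exception would contradict it.
- **The motive is weak.** Women unwilling to take a placebo are assigned to a suitable group without randomisation, and those randomised between Gutboost and Gutless are blinded. The article also encourages stable treatment. This stands as a reason to expect low use, and similar use in both arms. It does not close the gap.
- **The permissive rule is deliberately pragmatic.** The pragmatism described under recruitment concerns accommodating preferences when women are allocated. The article already expects participants to use the study brand, so barring a second probiotic fits its approach. Allocation to probiotic or placebo on top of ordinary care is a valid question, but it differs from the omega-3-alone comparison the article describes.

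**Conclusion.** The concern holds in a limited form. As written, the plan permits a woman in Gutless to start a non-study probiotic after allocation, and that would weaken the meaning of Gutboost versus Gutless. The likely effect is dilution of unknown size. The 90% and 80% figures rest on assumed use of 10% and 20% in Gutless, an own product as effective as the study product, and no effect on Gutboost.

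Two stronger readings are not supported. A reader might infer that the contrast is bound to be diluted or is invalid; the article gives no usage rate, and equal use with additive effects would leave the contrast intact. A reader might also see a safety problem in own omega-3 on top of the study dose; The safety profile of supplements cites trials of 1–6 g/day without a significant difference from placebo in safety, and both Gutboost and Gutless receive fish oil.

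Severity is low: the primary feasibility outcome is untouched, and the affected analyses are exploratory or belong to a conditional later stage.

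**What to change.** Add to the general rule in Concomitant therapies:

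*except that women in the intervention arms take no non-study probiotic or omega-3 supplement after allocation; any such use is recorded as a deviation and the woman stays in the intention-to-treat analysis; own use in the control arm is allowed and recorded.*

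This brings the rule into line with the switching criterion and with the stated contrast. It needs no new data collection, since use is already queried at every visit. The cost is a slightly less pragmatic trial and perhaps a few women deterred, which matters somewhat because recruitment is part of the primary outcome. It is best settled before women who may later count in an efficacy analysis are enrolled.
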